### Randomization

After successful completion of all baseline assessments participants are randomized 1:1 to the soccer intervention or control group. The randomization process will be conducted by a research consultant at The Copenhagen Trial Unit who has no other involvement in the study. The study flowchart is presented in Figure 1.

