### Study assessments

All assessments will take place at baseline, and after 12 weeks and 32 weeks. Measurement of body composition, peripheral vascular function, glucose tolerance, blood pressure, and blood markers will be performed in the morning after an overnight fast. Subjects will be instructed to avoid intake of medication, caffeine and vitamins, and to abstain from tobacco use for 12 h prior to the above mentioned tests and to avoid strenuous physical activities 48 h prior to all examinations.

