### Patient-reported outcomes

Information on socio-demographic and lifestyle characteristics will be collected at baseline [33]. Health-related quality of life outcomes will be measured using the eight sub scales of the Medical Outcomes Study Short Form [34] and the 15 subscales of the European Organization for Research and Treatment of Cancer (EORTC QLQ-C30) [35]. Diagnosis-specific symptoms and side-effects will be measured with the supplement EORTC QLQ-PR25. Anxiety and Depression will be measured with the two subscales of the Hospital Anxiety and Depression Scale [36,37]. Social support and network will be measured with The Multidimensional Scale of Perceived Social Support [38]. Leisure time physical activity level will be examined using a self-administrated questionnaire classifying patients in the following groups: I) sedentary; II) walking or cycling for pleasure; III) regular physical exercise at least 3 hrs per week; or IV) intense physical activity more than 4 hours per week. The Physical Activity Scale will be used to assess average weekly physical activity of sleep, work, and leisure time [39].

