### Statistical considerations

#### Sample size calculations

Since recreational soccer has not previously been applied as a rehabilitation strategy for men with PCa, the possible effect size on LBM is unknown. However, Krustrup et al. [41] have shown that the effect of soccer training on LBM is comparable to that of progressive resistance exercise [42]. In men with PCa undergoing ADT progressive resistance exercise has yielded increases in LBM of 0.7 kg after 12 weeks of training [15]. To detect a 0.7 kg difference in LBM between the groups, assuming a standard deviation (SD) of 1.0 kg, 34 patients are needed in each group with a significance level (two-sided) of 5% and a power of 80%. Due to possible dropouts we plan to include 40 patients in each group.

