#### Data analyses

Data entry will be undertaken using a secure web server and statistical analysis will be performed using Statistical Analysis Systems (SAS) version 9.2. The statistician will prepare results with no knowledge of the randomization coding. The primary endpoint will be reported as a two-sample t-test comparing change scores in the two randomization groups. Significance level will be set at 0.05.

Regarding secondary outcomes, the continuous variables, i.e., VO_2_max, HRmax, waist and hip circumferences, CMJ, and stair climbing parametres, and the patient reported outcomes, respectively, will be reported as either means with corresponding 95% confidence limits or as medians and interquartile range (IQR). For count data, i.e., the Flamingo balance test and the sit-to-stand test, Poisson regression will be used, and categorical data, i.e., single questionnaire items, will be reported as proportions and compared across randomization groups using chi-squared tests or logistic regression.

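### The plan allows ordered single questionnaire items to be compared by a chi-squared test that ignores their order and the baseline answer, and does not say that the logistic alternative is ordinal or baseline-adjusted

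*Protocol article*

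**What the plan says.** Under Data analyses, the article sets the method for this type of outcome: "categorical data, i.e., single questionnaire items, will be reported as proportions", and these are to be "compared across randomization groups using chi-squared tests or logistic regression". It gives no rule for choosing between the two methods, does not say whether the logistic model is binary or ordinal, and mentions no baseline covariate.

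Under Patient-reported outcomes, the leisure-time activity questionnaire is described as "classifying patients in the following groups: I) sedentary; II) walking or cycling for pleasure", followed by class III (regular exercise) and class IV (intense activity). The classes run from least to most active.

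Under Study assessments: "All assessments will take place at baseline, and after 12 weeks and 32 weeks". Under Randomization, allocation follows completion of the baseline assessments. The baseline answer should therefore exist for every randomised man.

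**The concern.** A Pearson chi-squared test on a four-class item has 3 degrees of freedom and gives the same result if the classes are shuffled. A training programme would be expected to move activity in one direction, and the test makes no use of direction. It also discards the baseline answer, whereas the primary analysis uses baseline through change scores.

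At stake is the chance of detecting real shifts in ordered items in a trial of 80 men, and of correcting chance baseline imbalance in them. Validity is not at stake: in simulation the type I error was close to 5% for every method compared.

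**Working it through.** **1. The plan's own figure.** The only power statement concerns lean body mass. The Sample size calculations section takes a difference of 0.7 kg and an SD of 1.0 kg, and arrives at 34 men per arm for 80% power at the two-sided 5% level. The normal approximation gives n = 2 × (1.960 + 0.842)² × (1.0/0.7)² = 2 × 7.85 / 0.49 = 32.04, so 33 per group. With the exact noncentral t distribution, 33 per group gives 79.97% power and 34 gives 81.2%, so 34 is right. Then 34 / 0.85 = 40, which matches the planned 40 per group. The figure reproduces. There is no corresponding figure for single questionnaire items.

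**2. Order alone, large-sample check.** Give a 1-df trend test and a 3-df chi-squared test the same noncentrality. At 80% power for the 1-df test this is (1.960 + 0.842)² = 7.85.

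| 1-df trend test | 3-df chi-squared | Relative loss |
|---|---|---|
| 50% | 34.5% | 1 − 34.5/50 = 31% |
| 80% | 64.5% | 1 − 64.5/80 = 19% |
| 90% | 78.4% | 1 − 78.4/90 = 13% |

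**3. Simulation at the trial's size.** Taken from the article: 34 per group, 1:1 allocation, two-sided 5%. Assumed, because the article gives none of it: four or five classes, flat or skewed answers, a common odds ratio (OR) of 2, 3 or 4, and a latent baseline correlation of 0.3, 0.5 or 0.7. There were 3,000 runs per setting. The ordinal test is the Wilcoxon test, which is the score test of the proportional-odds model. Rank ANCOVA stands in for the baseline-adjusted ordinal model. Relative loss = 1 − power(chi-squared) / power(comparator).

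Example: four classes at 40/35/20/5%, correlation 0.5.

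| OR | Chi-squared | Two-level split | Ordinal | Ordinal + baseline | Loss, order alone | Loss, order + baseline |
|---|---|---|---|---|---|---|
| 2 | 21.4% | 27.7% | 33.5% | 40.1% | 36% | 47% |
| 3 | 50.9% | 53.5% | 68.7% | 76.2% | 26% | 33% |
| 4 | 72.4% | 69.1% | 86.8% | 92.3% | 17% | 22% |

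The two-level split shows what an unadjusted binary analysis would give. It too falls short of the ordinal test.

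Relative loss across all assumed settings:

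| OR | Order alone, 4 classes | Order alone, 5 classes | Order + baseline, 4 classes | Order + baseline, 5 classes |
|---|---|---|---|---|
| 2 | 35–37% | 41–45% | 37–58% | 44–64% |
| 3 | 25–27% | 32–33% | 29–41% | 35–48% |
| 4 | 15–17% | 21–22% | 17–25% | 23–28% |

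A separate simulation with 36 per arm and a uniform shift agrees. Chi-squared against ordinal plus baseline gave 32–38% against 56–74% at OR 2.5, and 58–67% against 81–95% at OR 3.5.

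**4. When the shift is not uniform.** If training mainly moves men into class III, the ranking can change. With control 40/30/20/10% and soccer 25/20/45/10%, chi-squared has 48% power and the unadjusted rank test 43%. With 25/50/20/5% against 20/30/45/5%, the figures are 48% and 36%. Under shifts of this kind, the baseline-adjusted ordinal test ranged from slightly below chi-squared (44% against 49%) to clearly above it (59% against 47%).

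**The case against.** The strongest reply is that logistic regression is one of the two named methods. A proportional-odds model is a logistic regression and can carry the baseline answer, so the wording already permits the remedy. A condensed article may also leave the exact model to an analysis plan that is not shown. This stands as far as it goes. A reader might infer that the plan prescribes chi-squared for these items, or that its logistic model must collapse them to two levels; the text says neither. What remains is that the article does name methods, and one of them is order-blind and takes no account of baseline for data it describes as ordered.

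The scope is also narrow. Data analyses groups the patient-reported outcomes with the continuous variables, summarised by means or medians, and most of the instruments are scored as subscales. A reader might infer that quality-of-life results in general are affected; the documents do not support that. The leisure-activity item is the one ordered single item that the article sets out.

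For that item a uniform shift may not be the right model. By the Intervention group section, weeks 9–12 hold three sessions of 15 + 3 × 15 = 60 minutes, or 3 hours a week, which is the class III threshold. A shift concentrated in class III is plausible, and step 4 shows that the gain may then disappear.

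Sparse tables are not a dependable argument. If 10% of men are in the top class, the expected count with 36 per arm and no effect is 36 × 0.10 = 3.6, below 5; with flat answers it is 36 × 0.25 = 9. With control answers of 40/30/20/10%, some expected count below 5 occurred in 84–99% of tables under no effect or a downward shift, but in only 8–25% under an upward shift. Type I error stayed near 5%.

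**Conclusion.** The point holds as a modest efficiency issue. The article permits an order-blind test without baseline adjustment for ordered items, and does not state that its alternative is ordinal or baseline-adjusted. Under an assumed proportional-odds shift with 34 to 36 men per arm, the relative power loss is roughly 17–64% when order and baseline are both ignored. For order alone it is about 15–37% with four classes. It shrinks as the effect grows, and can vanish or slightly reverse when the shift sits in one class.

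A reader might infer a single headline such as a third to a half. That fits only ORs of about 2 to 3 with a baseline correlation near 0.5, and needs order and baseline combined. The article supplies none of these inputs, so the range and its assumptions should be given instead. The loss from ignoring order does not apply to yes/no or unordered items. The primary t-test and the 34 (40) per group are untouched.

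**What to change.** Add one sentence to Data analyses: ordered single items will be analysed by proportional-odds (ordinal logistic) regression of the follow-up answer on randomised group and baseline answer, reporting the common odds ratio with its 95% confidence interval. Keep chi-squared or Fisher's exact test for unordered items. Continue to report the proportion in each class, as already planned, so that a shift concentrated in one class remains visible.

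The cost is that sentence and a standard procedure in the software already named. No extra data are needed. The downside is reliance on the proportional-odds assumption, which may be doubtful for the activity item.

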## Discussion

Adverse treatment side-effects of ADT for PCa patients include loss of LBM, increased fat percentage and increased risk of myocardial infarction [11], fractures [43] and diabetes [10], as well as reduced QoL [44]. Interventions aimed at mitigating these side effects are both warranted and important for patient well-being [14].

The current study will provide a comprehensive investigation into the effects of a relatively brief (12 weeks) and medium-term (32 weeks) exposure to physical exercise on numerous physiological outcomes including body composition, cardiovascular function, bone health, insulin sensitivity, mobility, muscle strength, balance and patient reported outcomes such as QoL in PCa patients undergoing ADT. Recreational soccer will be used as a unique and novel rehabilitation initiative and, to the best of our knowledge, this is the first time soccer has been proposed as a complementary intervention in the treatment of cancer. This is also the first study to examine cardiac function in PCa patients with comprehensive echocardiography, and to monitor the impact of exercise training in PCa patients on cardiac function and peripheral vascular function. Animal studies have provided evidence that exercise training may counteract left ventricular dysfunction associated with ADT in rodents [45]. Our study is therefore likely to provide important and novel information about cardiovascular health in PCa patients undergoing ADT.

The choice of soccer as an intervention is based on a number of considerations. Firstly, participation in sport is increasingly recognized as important for public health [46] and recent evidence from a large prospective cohort study shows that participation in organized sport is associated with reduced mortality (hazard ratio = 0.71; 95% CI = 0.56, 0.91) [47]. Secondly, soccer is considered the most prominent team sport in the world, with more than 270 million active sports club players [48] and most Danish men have played the game. Thirdly, recent studies have shown that recreational soccer induces beneficial musculoskeletal, metabolic and cardiovascular adaptations in healthy untrained young men [49], middle-aged men with hypertension [50,51], premenopausal women [52] and middle-aged men with type 2 diabetes [29]. The positive effects obtained after 12–14 weeks of soccer training in the studies with healthy untrained young men and premenopausal women were maintained with a reduced training volume beyond a one-year period following the intervention [53,54]. Mean heart rates of 80-85% of HRmax and numerous (>190/h) high intensity actions, i.e. dribbles, shots, turns, jumps, sprints, accelerations, decelerations and tackles, may explain why soccer effectively stimulates both aerobic and anaerobic energy delivery systems [55,56]. In relation to bone health, a topic of particular concern in the PCa population, studies have found that 12–14 weeks of soccer training significantly increases lower extremity bone mass [49] and volumetric BMD in the tibia [52] and results in marked increases in plasma levels of osteocalcin [57]. Intense and diverse movements resulting in the generation of large ground reaction forces are hypothesized to account for these adaptations, as they represent near optimal osteogenic stimuli [58]. Further evidence of the favourable musculoskeletal potential of soccer movements comes from demonstration that the activity pattern and high intensity actions involved in soccer training provide marked increases in lower extremity [49,54] as well as upper body LBM [53], and that the whole-body muscle hypertrophic effects of soccer are greater than for continuous running and interval running, and as effective in increasing LBM as resistance exercise [59]. With regards to the cardio respiratory fitness effects of soccer, it has been shown that short-term soccer training was greater [60,61] or equal to [62] training volume-matched continuous running programs, and similar to the effects of high-intensity interval running [63]. Interestingly, soccer training was perceived as less exhausting than both continuous and intermittent running in young healthy men [40]. Recreational soccer therefore may constitute a highly motivating exercise-based rehabilitation intervention. Importantly, soccer training also provides peer-based psychosocial support and added individual social capital [64], which is likely to contribute to long-term adherence to training. Of note, the above-mentioned studies investigated men and women aged 18–55 years. Less information is available about the effects of soccer training for elderly (>65 years) subjects but recent studies have shown that heart rate is also high for elderly soccer players during small-sided games [56] and cross-sectional studies have provided evidence of elderly soccer players’ impressive cardiovascular and musculoskeletal health profiles, with rapid muscle force and postural balance scores equal to those of 30 years-old untrained men [65].

One particular aim of this study is to address whether an out-door intervention with little need for equipment can achieve effect sizes comparable to those of multimodal interventions requiring relatively expensive training facilities, i.e. resistance exercise machines and stationary bicycles. With a low cost to benefit ratio, potential positive results from the study may be disseminated to a broader population of men with PCa, in co-operation with existing community-based soccer clubs. This could potentially make an important contribution to the cancer care pathway for PCa patients and make a significant, positive impact on PCa survivorship both short- and long term.

Finally, a goal of the current research project is to build a bridge between the clinical environment and the existing expertise within exercise- and sports psychology and physiology in order to meet the legitimate demands from male cancer survivors for patient-centered and action-orientated interventions aimed at improved health [66]. Collaboration between health care specialties, i.e., oncology, urology, cardiology, psychology, physiotherapy and exercise physiology in the current study is crucial for its success and the results are likely to benefit the care and rehabilitation of PCa patients with possible favorable effects on long-term clinical outcomes.

## Abbreviations

ADT: Androgen deprivation therapy; BMC: Bone mineral content; BMD: Bone mineral density; DXA: Dual-energy X-ray absorptiometry; IVST: Interventricular septal wall thickness; LBM: Lean body mass; LV: Left ventricular; LVEDD: Left ventricular end-diastolic diameter; LVID: Left ventricular internal dimension; OGTT: Oral glucose tolerance test; PAT: Peripheral arterial tonometry; PCa: Prostate Cancer; PWT: Posterior wall thickness; QoL: Quality of life; RER: Respiratory exchange ratio; RHI: Reactive hyperemic index; RM: Repetition maximum; TDI: Tissue doppler Imaging; VO2max: Maximal oxygen uptake.
